### Safety monitoring

To protect the rights and interests of patients, all patients will be informed of the potential benefits and risks of the trial before they enroll. After confirming that the patient understands the relevant content, we will ask the patient to sign an informed consent form. Patients who do not sign the informed consent form will not be admitted to the study.

Acupotomy may trigger adverse events, including dizziness and local hematoma. If dizziness occurs during treatment, the doctor will stop the treatment immediately. Then, the doctor will lay the patient down on the pillow and provide warm water. If hematoma occurs, the patient will be instructed to apply a local cold compress and switch to a hot compress after 24 h to promote dissipation and absorption of the blood. If an adverse drug reaction occurs, the drug will be discontinued. Active clinical observation and symptomatic treatment will be carried out.

The Ethics Committee of the First Affiliated Hospital of Guangzhou University of Chinese Medicine will monitor the safety of this trial and provide advice (e.g., endpoint adjustment) if necessary. When an adverse event occurs in a patient, the researchers will record the details, such as the time, severity, duration, treatment measures, and event outcomes. The responsible doctor will determine the causal relationship between the treatment method and the adverse event and decide whether the patient will be allowed to continue the study. Relevant information will be reported to the ethics committee on the same day.

The following are the criteria for terminating a patient from the study: (1) the patient has experienced a serious adverse event, the patient has requested to suspend participation in the trial, or the trial operator believes that it is necessary for the patient to be terminated from the trial; (2) during the study, the patient is found to have a systemic disease that could not be detected before the start of the clinical trial; (3) for other reasons, the researchers believe that the patient is not suitable for continued treatment; and (4) the patient has privately received other interventions that may affect the outcomes.

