**Fig. 2 Fig2:**
[figure not shown]
Needle-knife

The incision line will be consistent with the longitudinal axis of the lower limb. The body of the needle-knife will be perpendicular to the skin. The doctor will operate according to the following procedural steps: point fixation, orientation, pressure application, and penetration. When the needle-knife reaches the target depth, the doctor will perform a manual operation. The details of the manual operation are presented in Additional file 2. After the operation, the needle-knife will be pulled out, and local hemostasis will be applied for 3 min. The wound will be disinfected with iodine and dressed with a band aid. Patients will receive 2 acupotomy sessions for 2 weeks (once a week).

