### Blinding

This study will follow a single-blind approach. The operators will perform a mock standard acupotomy procedure in the sham acupotomy group. The operators will pierce through the skin only and not stimulate the relevant ligaments and muscles. The needle-knife will stay under the skin for 10 s without any manipulation. At the same time, others involved in this experiment will be blind to the group allocation (data administrators, biostatisticians, programmers, measurement evaluators, etc.) to minimize performance bias.

To protect the rights of the subjects, we will approve free acupotomy for patients in the sham acupotomy group at the end of the trial.

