### Statistical analysis

Per-protocol subject analysis and intention-to-treat analysis will be used to analyze the efficacy. The safety analysis set will be used to perform the safety evaluation.

We will develop a statistical analysis plan with a statistician. The statistical software package R 3.4.3 will be used to perform a descriptive statistical analysis, exploratory analysis, and dropout analysis. The results will be considered statistically significant when the *P* value is less than 0.05. In the intention-to-treat analysis, when data are missing, the last observation will be used for interpolation. Then, we will perform a sensitivity analysis for the result.

For continuous variables that follow or meet the assumptions of a normal distribution and homogeneity of variance, we will use Student’s *t* test; otherwise, the Mann-Whitney test or Wilcoxon test will be used. A chi-square test will be performed for discrete or categorical variables. When analyzing data obtained by repeated measurements, we will use analysis of variance or analysis of covariance.

For the safety analysis, we will first perform a descriptive analysis. Subsequently, the incidence of adverse reactions will be compared between the two groups using a chi-square test. Causality will be considered in the comparison regarding the severity of adverse reactions and the needle-knife operation. If there are a large number of adverse reactions, the relationship between the intervention time and baseline characteristics will be analyzed. We will use the correlation coefficient to analyze these relationships.

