This study will have some limitations. First, we will only enroll patients with level I-III KOA; thus, we will not be able to observe the effect of acupotomy on KOA of other levels in patients. Second, we selected a relatively short-term follow-up period for evaluating a chronic arthritis condition, preventing the monitoring of long-term effects. Third, this will be a single-blind study, which means we will not be able to avoid caregivers’ impact. Furthermore, as we will use the last observation carried forward method to interpret findings, if the rate of missing data is high, the stability of the data analysis results after interpolation will become low, potentially even distorting the results of the original data analysis due to bias. Last, this study will be performed in China, so the conclusion may not be suitable for application in patients of other ethnicities.

In summary, we will perform a parallel, block-randomized, single-blind, sham-controlled trial to evaluate the efficacy and safety of acupotomy in KOA patients.

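### The one between-arm safety test named counts adverse reactions, an undefined term that may depend on a causality call by a doctor not clearly stated to be blind

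*Protocol article*

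**What the plan says.** All places are in the protocol article.

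- **Recording (Safety monitoring).** Collection is not filtered by cause: "When an adverse event occurs in a patient, the researchers will record the details".
- **Attribution (Safety monitoring).** The next step is a causality judgement: "The responsible doctor will determine the causal relationship between the treatment method and the adverse event". The same doctor decides whether the patient continues.
- **Test (Statistical analysis).** After a descriptive analysis whose event class is not given, "the incidence of adverse reactions will be compared between the two groups using a chi-square test".
- **Further use of causality (Statistical analysis).** "Causality will be considered in the comparison regarding the severity of adverse reactions and the needle-knife operation".
- **Blinding (Blinding).** After describing what the operators do in the sham arm, the section says that "others involved in this experiment will be blind to the group allocation (data administrators, biostatisticians, programmers, measurement evaluators, etc". The bracket is left open-ended, and no treating or responsible doctor appears in it.
- **Who the doctor is (Intervention, Acupotomy group).** The person doing the procedure is called by the same word: "The doctor will operate according to the following procedural steps".
- **Limitations (Discussion).** "this will be a single-blind study, which means we will not be able to avoid caregivers’ impact".

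**The concern.** Safety monitoring speaks of adverse events for what is recorded, and of an adverse drug reaction for harm attributed to the drug. Statistical analysis then names adverse reactions for the between-arm test. Taken literally, the numerator of that test is what remains after a causality judgement made once treatment has been allocated.

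Randomisation supports a comparison of all recorded events. It does not support a comparison of events selected after allocation by someone who may know the arm. Such a doctor might attribute an ambiguous event, such as dizziness, more readily to the full procedure than to a ten-second skin puncture, or might discount it. The bias could run either way. A false safety signal, or a missed one, could then come from labelling alone. The preceding descriptive analysis does not settle this, because its event class is not stated.

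**Working it through.** **The plan's own figure.** The protocol gives no number for the safety comparison. Its sample size serves only to fix the arm sizes, and it reproduces. With a difference of 2.14, SD 4.19, two-sided 5% and 80% power, the normal approximation gives 61 per arm (122). The t-test calculation gives 61.15, rounded up to 62 per arm (124, as stated). Enrolling 136 at 1:1 gives 136/2 = 68 per arm.

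**Inputs from the document.** 68 per arm; chi-square test; significance level 0.05 (two-sided assumed, since sidedness is not stated).

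**Inputs assumed, because the document gives none.** The true risk of an adverse event, and the share of those events called related in each arm.

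**Formula.** Proportion counted as adverse reactions = true event risk × share called related. The probability of P<0.05 is the sum of the two binomial probabilities (n = 68 each) over all tables for which the uncorrected chi-square test rejects.

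**No true difference between arms**

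| True risk, both arms | Share called related, acupotomy v sham | Proportions tested | Probability of P<0.05 |
|---|---|---|---|
| 10% | 90% v 90% | 9% v 9% | 5.2% |
| 10% | 90% v 70% | 9% v 7% | 7.3% |
| 10% | 90% v 50% | 9% v 5% | 14.8% |
| 20% | 90% v 90% | 18% v 18% | 4.9% |
| 20% | 90% v 70% | 18% v 14% | 9.5% |
| 20% | 90% v 50% | 18% v 10% | 26.5% |
| 30% | 90% v 90% | 27% v 27% | 5.0% |
| 30% | 90% v 80% | 27% v 24% | 6.9% |
| 30% | 90% v 70% | 27% v 21% | 13.0% |
| 30% | 90% v 50% | 27% v 15% | 40.7% |

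Comparing all events instead (30% v 30%) gives 5.1%.

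**A true excess, 30% acupotomy v 10% sham**

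| Share called related, acupotomy v sham | Proportions tested | Power |
|---|---|---|
| all events compared | 30% v 10% | 85% |
| 90% v 90% | 27% v 9% | 80% |
| 60% v 90% | 18% v 9% | 33% |
| 50% v 90% | 15% v 9% | 19% |

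Equal attribution does little harm: the false-positive rate stays near 5%, and power falls from 85% to 80%. The problem arises only when attribution differs by arm.

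**The case against.** Four arguments stand against the point.

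**The term may be loose.** Adverse reactions is nowhere defined and may simply mean the recorded adverse events. The later sentence bringing causality into the severity comparison would be partly redundant if the numerator were already restricted to attributed events. This stands. On that reading there is no filter and only the wording needs repair, but it is the same repair.

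**The doctor may be blind.** A reader might infer that the protocol shows the causality judge to be unblinded. It does not. The Blinding section covers others involved in the trial and its list is open-ended, so the responsible doctor could be included. The termination criteria also mention a trial operator, perhaps a separate role. Against this, the operator is called the doctor under Intervention, and the Discussion concedes caregivers' influence. The text leans towards an unblinded caregiver without saying so.

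**Other tests are possible.** Statistical analysis also has a general chi-square line for categorical variables, which could cover any adverse event, and a separate statistical analysis plan is announced. So the test on adverse reactions is the only safety test named, which is not to say that it is the only one that will be run.

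**The sizes rest on assumed rates.** This also stands. Sham treatment pierces the skin too, and nothing in the document supports a 50% attribution share in that arm. Smaller gaps matter little: 90% v 80% at a 30% risk gives 6.9%. Nor does reversed labelling hide an excess to the same degree as it creates one. Hiding is a loss of power, a different quantity from a false-positive rate.

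**Conclusion.** The point holds in a conditional form. The only between-arm safety test named rests on an undefined term whose literal meaning depends on a causality judgement, and the protocol does not clearly state that the person making it is blind. Bias arises only if three things are true together: the term means attributed events, the doctor knows the arm, and attribution differs between arms. The document establishes none of these outright.

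Under those conditions and the assumed rates, the false-positive rate ranges from little above 5% for small labelling gaps to 41% for the most extreme one shown. Power for a true 30% v 10% excess could fall from 85% to 19%. These figures show that the mechanism can matter. They do not forecast what this trial will find.

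This is an inexpensive improvement to a supportive safety analysis. The WOMAC primary outcome is unaffected.

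**What to change.** In Statistical analysis, make the main between-group safety comparison the proportion of patients with any adverse event regardless of judged cause, also shown by type and severity. Keep doctor-attributed adverse reactions as a descriptive secondary table, and define the term there. It would also help to say in Blinding whether the responsible doctor knows the allocation.

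The cost is a change of wording. Safety monitoring already has every event recorded with its details, so no further data collection is needed, and the main comparison no longer depends on a causality review.

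There are two limits. Unrelated events add some noise to the comparison. The change also does not remove bias from unequal noticing or recording of events: the false-positive rate of about 5% for all events assumes that they are recorded alike in both arms.

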**Trial evaluation**						
Informed consent	√					
Adverse event			√	√		
Safety evaluation			√	√		

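### Leaving the study is not separated from stopping treatment, so leavers' month-3 and month-6 scores are filled by LOCF; and Table 2 schedules no adverse event assessment after W7

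*Protocol article*

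**What the plan says.** **Exit rules.** The relevant list in Safety monitoring opens: "The following are the criteria for terminating a patient from the study: (1) the patient has experienced a serious adverse event". The same item adds the patient's own request and the operator's judgement. Item 3 covers cases where "the researchers believe that the patient is not suitable for continued treatment", which concerns treatment although it stands in a list about leaving the study. The last item is "4) the patient has privately received other interventions that may affect the outcomes". After any adverse event, the responsible doctor is also to "decide whether the patient will be allowed to continue the study". The article does not say whether outcomes are still collected once one of these criteria is met.

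**Follow-up.** The Intervention section gives two weekly sessions, while Table 2 shows a treatment period of W1-W6; these two need reconciling. WOMAC (primary) and VAS are measured at baseline, 1 week after the end of treatment (W7), and at 3 and 6 months.

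**Missing data.** Statistical analysis states: "In the intention-to-treat analysis, when data are missing, the last observation will be used for interpolation". A sensitivity analysis and a dropout analysis are also planned.

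**Adverse events.** In Table 2 the rows "Adverse event" and safety evaluation are ticked for Treatment and W7 only. The Safety monitoring text says that details of an event are recorded when it occurs, with no end date.

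**The concern.** An intention-to-treat comparison at month 3 or month 6 needs the scores of patients who had a serious adverse event or turned to other treatment. For most of the follow-up no session remains to be stopped, so ending participation then mainly costs data. Seeking treatment elsewhere plausibly reflects poor response and may differ by arm, so the gaps are likely to be informative. LOCF fills them with a score from before the event. A later analysis can vary that assumption but cannot recover scores that were never collected.

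The second issue is separate. The Discussion gives efficacy and safety as the aim, and patients are contacted at M3 and M6 anyway, yet the schedule asks about adverse events at neither contact. Late or persisting effects of an invasive procedure would depend on someone happening to report them.

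**Working it through.** **1. The plan's own figures (Sample size).** Mean changes are 16.34 and 14.2, a difference of 2.14, with SD 4.19, alpha 0.05 (taken as two-sided) and 80% power. A t-based two-sample calculation gives 61.15, so 62 per arm and 124 in total, as stated. Then 124 × 1.10 = 136.4, which gives the stated 136, or 68 per arm. The sample size is not in question here.

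**2. Effect of LOCF at month 6.** The document gives no exit rates, so these are assumptions:
- Half the gain is lost by month 6. True means are 16.34/2 = 8.17 (acupotomy) and 14.2/2 = 7.10 (sham), a true difference of 1.07.
- Exits occur after W7, at 5% in one arm and 15% in the other. That is 68 × 0.05 + 68 × 0.15 = 13.6 patients, or 13.6/136 = 10% overall, equal to the plan's own dropout allowance.
- Leavers' true month-6 mean equals that of their arm.
- Leavers had a fraction k of the average 1-week gain, and LOCF carries that value forward.

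For exit rate p, the LOCF mean in an arm is (1 − p) × (true month-6 mean) + p × k × (1-week gain).

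| Exit rate, acupotomy / sham | k | Acupotomy | Sham | Difference shown | Shift from 1.07 |
|---|---|---|---|---|---|
| 5% / 15% | 1 | 0.95×8.17 + 0.05×16.34 = 8.58 | 0.85×7.10 + 0.15×14.2 = 8.17 | 0.41 | −0.66 |
| 5% / 15% | 0.5 | 0.95×8.17 + 0.05×8.17 = 8.17 | 0.85×7.10 + 0.15×7.10 = 7.10 | 1.07 | 0 |
| 5% / 15% | 0 | 0.95×8.17 = 7.76 | 0.85×7.10 = 6.04 | 1.73 | +0.66 |
| 15% / 5% | 1 | 0.85×8.17 + 0.15×16.34 = 9.40 | 0.95×7.10 + 0.05×14.2 = 7.46 | 1.94 | +0.87 |

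Differences and shifts are taken before the arm means are rounded.

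**3. Adverse event window.** Taking 6 months as 26 weeks (an assumption), W7 falls at week 1 after treatment, so 26 − 1 = 25 weeks have no scheduled assessment. Counted from the start of treatment, the scheduled window is 3 of 28 weeks (11%) if treatment lasts 2 weeks, or 7 of 32 weeks (22%) if it runs W1-W6. The unscheduled period is 25 weeks either way.

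**The case against.** A reader might infer more than the document supports.

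- **That leavers drop out of the intention-to-treat analysis.** They do not. LOCF keeps them in; what is lost is their real later score.
- **That serious adverse events go unreported.** The triggering event is recorded with its severity, duration and outcome and reported to the ethics committee the same day. Nothing removes that patient from the safety set.
- **That adverse events after W7 are not recorded at all.** The recording sentence has no end date. Table 2 shows only that no assessment is scheduled, so the two places disagree and must be reconciled.
- **That the bias favours one arm, or spoils every comparison.** The table shows it shrinking the difference, vanishing or enlarging it. Exits after W7 leave the 1-week comparison largely untouched.

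There is also real mitigation. Permitted indomethacin cream does not trigger exit; only privately received interventions that may affect the outcomes do. A dropout analysis and a sensitivity analysis are planned, and the Discussion concedes that LOCF may distort results if much is missing. Finally, this is a condensed article, and the full protocol may provide for follow-up after treatment stops.

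These points narrow the concern but do not remove it. The article does more than leave a detail open: it states an exit rule worded as leaving the study and a schedule that ends adverse event assessment at W7. Neither can be repaired at the analysis stage.

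**Conclusion.** The point holds in this limited form. As written, the exit criteria merge stopping treatment with leaving the study, so patients who exit after the sessions have their month-3 and month-6 outcomes replaced by earlier values. The size is uncertain. With 10% exits overall, split unevenly, the month-6 difference shown ranges from 0.41 to 1.94 against a true 1.07, and one of the four scenarios shows no bias. Those figures rest on the assumed exit rates, the assumed half-loss of gain and leavers sharing their arm's true month-6 mean. They show that the direction cannot be known in advance and are not a forecast.

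The schedule gap of about 25 of 26 weeks rests only on Table 2 and on taking 6 months as 26 weeks. It concerns scheduled assessment, not a ban on recording. The change is worth making, but the point does not undermine the 1-week result or the capture of the serious adverse event that leads to exit.

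**What to change.** 1. Leave the clinical decisions on stopping treatment as they are. State separately that every randomised patient who has not withdrawn consent keeps the scheduled WOMAC and VAS contacts at 1 week, M3 and M6, whether or not treatment was stopped or other treatment was started.
2. Record other interventions in the CRF, and use the observed scores of these patients in the intention-to-treat analysis instead of values carried forward from before the event.
3. Tick adverse event and safety evaluation at M3 and M6 in Table 2, and bring the table and the recording sentence in Safety monitoring into agreement.

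The cost is protocol wording, a few CRF lines at contacts that already take place, and a little extra effort to follow patients who have stopped. The planned sample size does not change. If the full protocol already provides for this, one sentence and a corrected table are enough.

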### Statistical analysis

Per-protocol subject analysis and intention-to-treat analysis will be used to analyze the efficacy. The safety analysis set will be used to perform the safety evaluation.

We will develop a statistical analysis plan with a statistician. The statistical software package R 3.4.3 will be used to perform a descriptive statistical analysis, exploratory analysis, and dropout analysis. The results will be considered statistically significant when the *P* value is less than 0.05. In the intention-to-treat analysis, when data are missing, the last observation will be used for interpolation. Then, we will perform a sensitivity analysis for the result.

For continuous variables that follow or meet the assumptions of a normal distribution and homogeneity of variance, we will use Student’s *t* test; otherwise, the Mann-Whitney test or Wilcoxon test will be used. A chi-square test will be performed for discrete or categorical variables. When analyzing data obtained by repeated measurements, we will use analysis of variance or analysis of covariance.

For the safety analysis, we will first perform a descriptive analysis. Subsequently, the incidence of adverse reactions will be compared between the two groups using a chi-square test. Causality will be considered in the comparison regarding the severity of adverse reactions and the needle-knife operation. If there are a large number of adverse reactions, the relationship between the intervention time and baseline characteristics will be analyzed. We will use the correlation coefficient to analyze these relationships.

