### Sample size

Referring to a previous study [27], we determined that the change in the WOMAC after compared with before treatment in the acupotomy group was 16.34 ± 4.19, and the change in the WOMAC after compared with before treatment in the sham acupotomy group was 14.2 ± 4.19; thus, the effect size was 2.14 [28]. The sample size should provide 80% statistical power at a significance level of 0.05.

We calculated a sample size of 124 with a repeated measurement design using the SAS software package (version 9.4, Tokyo, Japan). Considering a dropout rate of 10% during the research, we decided to enroll 136 participants.

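### Last observation carried forward in the intention-to-treat analysis gives early dropouts a WOMAC change of 0, which costs power and, if early loss differs by arm, biases the comparison

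*Protocol article*

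**What the plan says.** The Statistical analysis section plans both per-protocol and intention-to-treat efficacy analyses and fixes the missing-data rule for the second: "In the intention-to-treat analysis, when data are missing, the last observation will be used for interpolation". A sensitivity analysis is to follow. The limitations in the Discussion name the method, "as we will use the last observation carried forward method to interpret findings", and accept that it could distort the results if much data is missing.

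Under Outcome measurement and in Table 2, WOMAC, the primary outcome, is taken at baseline, 1 week after the end of treatment, and 3 and 6 months after it. There is no WOMAC between baseline and the 1-week visit.

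The Sample size section gives the expected changes. For the active arm it states: "the change in the WOMAC after compared with before treatment in the acupotomy group was 16.34 ± 4.19". The corresponding sham figure is 14.2, with the same SD. On dropout it says: "Considering a dropout rate of 10% during the research, we decided to enroll 136 participants". It does not say when the dropout occurs or how it divides between the arms.

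**The concern.** Carrying the last value forward assumes that a patient's score stays where it was last seen. Two things follow from this visit schedule.

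- **Loss before the 1-week visit.** The only value to carry is the baseline, so the imputed change is exactly 0. The plan expects both arms, sham included, to improve by 14 to 16 points with an SD of about 4. A few zeros in such data shrink the mean difference slightly and inflate the variance a great deal.
- **Loss after the 1-week visit.** An early post-treatment value stands in for the 3- or 6-month result, whatever happened in between.

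If early loss is equal in the two arms, the cost is power. If it is unequal, the arm with fewer zeros looks better even when the treatments do not differ. Unequal loss is possible here. The criteria under Safety monitoring for terminating a patient include serious adverse events, the operator's judgement and outside treatment. The operators know which procedure they performed.

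**Working it through.** **Inputs (Sample size and Randomization sections).** Mean change m = 16.34 (acupotomy) and 14.2 (sham), SD 4.19 in both, allocation 1:1, 136 enrolled (68 per arm), 10% dropout over the study. The significance level is 0.05, taken as two-sided because that reproduces the stated N.

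**The plan's own figure.** The difference is 16.34 − 14.2 = 2.14, or 2.14/4.19 = 0.511 SD. A two-sample t test at 80% power needs 61.15, so 62 per arm, or 124 in all, as stated (power 80.5%). For dropout, 124 × 1.1 = 136.4 and 124/0.9 = 138, so the stated 136 is within two patients of either.

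**Comparator without imputation.** With 10% of 68 left missing and unrelated to outcome, 61.2 per arm remain and power is 80.0%. With no loss at all it is 84%.

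**Distance of the imputed value.** 16.34/4.19 = 3.9 SD and 14.2/4.19 = 3.4 SD.

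**Effect of carrying baseline forward.** Let a share p of an arm be lost before the 1-week visit. With those changes set to 0:

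- arm mean = (1 − p)m
- arm variance = (1 − p) × 4.19² + p(1 − p)m²

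At p = 0.10 in both arms:

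- difference = 0.9 × 2.14 = 1.93
- acupotomy SD = √(0.9 × 17.56 + 0.09 × 267.0) = 6.31
- sham SD = √(0.9 × 17.56 + 0.09 × 201.6) = 5.83
- standard error = √((6.31² + 5.83²)/68) = 1.04
- difference/standard error = 1.85, and power is 45% (simulation also 45%)

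**Power by how much of the loss is early** (t test on change at the first post-treatment visit, 68 per arm, equal loss in the arms):

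| Early loss per arm | Assumption behind it | Power |
|---|---|---|
| 1.1% | 10% spread evenly, first visit at week 3 of 28 (2-week treatment in the Intervention section) | 78% |
| 2% | illustrative | 74% |
| 2.2% | 10% spread evenly, first visit at week 7 of 32 (Table 2 timing) | 73% |
| 3.3% | one third of the 10% | 68% |
| 5% | half of the 10% | 61% |
| 10% | all of the 10% | 45% |

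The two treatment lengths behind the 1.1% and 2.2% rows come from different parts of the article, which need reconciling. Both are shown and neither is preferred.

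If the zeros led to the article's rank-test fallback, power would be about 74% at 5% early loss and 63–64% at 10%.

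**Unequal early loss, no true effect** (14.2 in both arms, t test). The spurious difference is 14.2 × (difference in loss):

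| Assumed early loss | Spurious difference | Type I error |
|---|---|---|
| 10% vs 10% | 0 | 5% |
| 2% vs 4% | 0.28 | 6% |
| 5% vs 10% | 0.71 | 12% |
| 5% vs 15% | 1.42 | 29% |

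**Unequal early loss, true difference 2.14.** With 15% lost in acupotomy and 5% in sham, the difference is 0.85 × 16.34 − 0.95 × 14.2 = 0.40, with power about 7%. With 5% and 15% it is 0.95 × 16.34 − 0.85 × 14.2 = 3.45.

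**The case against.** **Timing of dropout.** A reader might infer from the 10% that power falls to 45% on the plan's own figures. It does not follow. The 10% runs to the 6-month follow-up, and patients lost after the 1-week visit carry a real post-treatment value, not a zero. The 45% is the worst case for equal loss at that rate; loss spread evenly over time gives 73% to 78%. This objection stands, so a range is reported.

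**Assumed imbalance.** The 29% type I error rests on 5% vs 15% early loss, which appears nowhere in the article. A small imbalance such as 2% vs 4% moves it only to about 6%. This also stands. The direction of the bias is certain, but its size is an assumption.

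**Choice of test.** The calculation uses a t test at one visit. The article names analysis of variance or covariance for repeated measurements, and a rank test when normality fails. The rank test loses less power. Power of the repeated-measures analysis under this imputation was not computed. The figures are therefore indicative.

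**Status of the analysis.** A reader might call this the headline result. The article lists per-protocol and intention-to-treat analyses together and does not say which is primary. Nor is the unnamed sensitivity method a fault, since that detail can sit in the statistical analysis plan, which is not shown.

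**Disclosure.** The authors acknowledge the risk, but tie it to a high rate of missing data. In this calculation 2% early loss, one or two patients per arm, already takes power below 80%. The admission does not change the method.

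**Conclusion.** The point holds with a limited size. The article itself fixes a rule that assigns zero change to anyone lost before the first post-treatment visit and freezes early values for later losses. At that visit, with 68 per arm and a t test on change, power lies between about 78% and 45%, depending on how much of the 10% dropout comes early, against about 80% if the same patients are left unimputed. The 80% assumes that loss is unrelated to outcome. Equal loss leaves type I error at 5%. Unequal loss favours the arm with less of it, by an amount that depends on an imbalance the article does not predict. This should be fixed, but it does not show that the trial will miss a real effect or report a false one.

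**What to change.** Remove last observation carried forward as the intention-to-treat method. Analyse all observed WOMAC values with a mixed model for repeated measures (arm, visit, arm-by-visit interaction, baseline WOMAC), and keep the carried-forward analysis at most as a sensitivity analysis. The same change should be made to the limitation in the Discussion.

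The cost is wording in the protocol and the statistical analysis plan; no visit, measurement or patient is added. The small downside is that the model relies on data being missing at random. The sensitivity analysis already promised can test that, for example by reference-based or delta-adjusted multiple imputation.
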